### Plans to promote participant retention and complete follow-up {18b}

The informed consent process allows time for consideration by both parents and discussion among family members. We provide participants with a trial information sheet that includes free-call phone numbers that can be used at any time. We provide instructions to participants if attending an EPI clinic outside the trial area that facilitates administration of vaccine according to the trial schedule.

At each visit, trial staff identify the infant and the group allocation, based on the trial sticker on the infant health card, residential location, and electronic vaccination record. Trial staff routinely record whether infants are migrating, or intend to migrate, within or out of the trial area. Administration of PCV by EPI staff follows the schedule allocated on the infant health card. Following administration of a dose of PCV, the date is recorded on the health card and in the electronic vaccination record.

Attrition bias due to the dropout of clusters is unlikely as this will require all five or six villages in a cluster to withdraw. Migration out of the trial area is limited; on average, only 10 children per cluster per year migrate out of the area. If clusters drop out, study power may be retained by increasing the number measured for the endpoint in each cluster. We will avoid the withdrawal of villages through close engagement with village representatives and continual informed consent.

### Data management {19}

A data management plan has been prepared and approved by the MRCG Head of Data Management and is available on request. Data are collected on eCRFs using a standardised format. Electronic data capture is done offline using encrypted devices which is then synchronised with a central server on a weekly basis. Trial staff attend all EPI clinics, confirming the identity of all infants and recording immunisation data in real-time. Trial staff generate source data on electronic devices at regular visits as per the trial timeline.

Data entered into eCRFs is monitored for completeness and consistency against the relevant source documents. Independent trial monitors undertake 100% verification of source data for the primary endpoints and informed consent. Anomalies identified are reconciled with the source.

Front-end data quality checks are programmed into the data capture application. Backend edit checks and validation checks are built-in to monitor the validity of data (e.g. to identify inconsistent dates and times, and clinical and antropometric measurements outside defined ranges, etc.). Data queries are generated weekly by the data manager for resolution by trial staff. Reports of data quality are generated periodically.

The trial database is housed on a secure network server with restricted access to the backend. The backend comprises a MSSQL database which will be regularly backed up as part of the organisation’s disaster recovery plan. An in-house web-based application is used for the database structure, using the PHP\ASP.Net platform connecting to the MSSQL backend database. A recovery point objective is set so that systems and data will be restored back 24 h prior to a failure. Daily and monthly backups of all media servers are done to achieve this objective.

The e-CRF is used as the specification for the design of the database. An annotated CRF indicates the relationship between the variable names in the database and the fields in the CRF. A data dictionary uses a standard template, including a list of database variable names, variable descriptions, data types, and sources, valid values, and in-built edit checks. Standard data coding will be used (e.g. latest MedDRA version accessed through the internet will be used for adverse event reporting).

The long term storage of research records is done in accordance with MRCG policies and procedures for archiving. All paper records will be held for at least 10 years in the Unit’s archiving facility. Data in electronic format will be held indefinitely on our Electronic Data Repository. The trial is run in compliance with the MRC Corporate Information Security Policy [50] and the Unit’s Information and Communication Technology Security Policy. The study is conducted in compliance with the ICH Harmonized Tripartite Guideline for Good Clinical Practice E6 (R2 Step 4).

### Confidentiality {27}

No subject identifiable information (names, addresses etc.) is entered into the trial database. Identifiable information is stored in the electronic medical record, vaccination and BHDSS databases, encrypted and password-protected, and accessible to limited staff involved in the care of patients. Trial monitors only access pre-specified, non-identifiable data. Informed consent documents are stored in locked, fire-resistant filing cabinets to which only the Principal Investigator and a limited number of delegated clinical trials personnel have access. Data are backed up at the end of each day in the field on encrypted flash drives to prevent any data loss during transit. All computers within MRCG are access controlled with strong password policies that prevent unauthorised access to networked user machines. Users to whom network access has been given are granted necessary privileges to the trial database based on their trial roles.

### Plans for collection, laboratory evaluation and storage of biological specimens for genetic or molecular analysis in this trial/future use {33}

The trial collects blood and NP specimens but procedures do not include genetic or molecular analyses of human material.

NP specimens are collected using flocked nylon swabs inserted into storage media which are then placed in a dry shipper for later transport to Basse. On isolated occasions when shippers are unavailable in the health facility, NP specimens are transported to the MRCG laboratory in Basse within 6 h. To culture NP specimens, a 10 μl loop of vortexed NP specimen is inoculated onto blood agar with 5% gentamicin and incubated in CO_2_. Identification of pneumococcal colonies follows recommended methods [46]. Specimens positive for pneumococcus undergo latex sweep serotyping in Basse. Morphologically different pneumococcal colonies are selected from the primary plate, purified, and stored. For internal quality control (QC), a proportion of NP specimens is processed by two different operators and results compared. External QC on sweep serotyping involves blind assessment of known spiked samples, prepared by the Murdoch Children’s Research Institute (MCRI) Pneumococcal Laboratory, placed among the routine specimens delivered to the laboratory. As further validation of the latex sweep serotyping, a proportion of the specimens that are positive for pneumococcus will be subjected to molecular serotyping microarray analysis by BUGS Bioscience at St George’s, University of London (SGUL). Microarray is the most sensitive method for detecting carriage of multiple pneumococcal serotypes; its specificity is similar to high-quality latex sweep [47]. The Basse laboratory undergoes external quality control for bacteriology according to One World Accuracy International (Burnaby, British Columbia, Canada).

An event of VT colonisation is defined as detection of pneumococcus in a NP specimen including serotypes 1, 3, 4, 5, 6A, 6B, 7F, 9 V, 14, 18C, 19A, 19F, or 23F, using latex sweep methods. All other serotypes will be defined as non-VT. Non-typeable isolates are defined as pneumococcal by colony morphology and biochemical means, or inability to serotype by the Quellung method.

According to the guideline for investigation, blood is collected for a rapid malaria test (0.02 ml), rapid haemoglobin measurement (0.02 ml), whole blood for plasma aliquot (1–2 ml), and blood culture (at most 3 ml). Obtaining 3 ml of blood in the blood culture optimises the detection of bacteraemia and thus the monitoring of safety in the trial. Blood will be collected using sterile technique and inoculated into culture bottles (Bactec Peds Plus). An automated system (Bactec 9050, Becton Dickinson) will be used for blood cultures. Bottles that signal positive will be sub-cultured onto blood agar, chocolate agar, and McConkey agar. Bottles which fail to signal within 5 days will be considered negative. Isolates grown will be identified using conventional microbiological techniques and biochemical tests (API, Biomerieux). Other sterile site samples will be processed using standardised techniques [48]. *S. pneumoniae* will be identified by colony morphology, susceptibility to ethylhydrocupreine and, if susceptibility is equivocal, by bile solubility, and reaction with polyvalent antisera (Statens Serum Institut, Copenhagen, Denmark). Isolates classified as contaminants will include coagulase-negative staphylococcus, bacillus species, micrococcus species, and *Streptococcus viridans*. Plasma aliquots will be stored and tested for antibiotic activity using a fully sensitive bacterial control strain. Invasive pneumococcal isolates are serotyped using a latex agglutination assay which employs factor and group-specific antisera (Statens Serum Institut, Copenhagen, Denmark).

## Statistical methods

### Statistical methods for primary and secondary outcomes {20a}

Coverage of each schedule during the course of the trial will be reported at the end of each of the four annual periods, as the proportion of surviving, resident children, who have completed the respective schedules at the ages of 12 and 18 months. Coverage calculations will be classified as receiving the respective schedules in a timely (completed before age 7 months [3 + 0] or 13 months [1 + 1]) or delayed fashion. Cross-over between groups will be defined as (a) change of residential location from a 1 + 1 to 3 + 0 cluster, and vice versa, for a period of 4 or more months and (b) receipt of the third dose of PCV at 8 months of age or greater in a 3 + 0 cluster.

The unit of inference will be the individual child. That is, we wish to estimate whether the risk of VT carriage in a child who lives in a geographic area using a 1 + 1 schedule is not greater than the given threshold when compared to a child in an area receiving the 3 + 0 schedule. The primary outcome will be presented as the proportion (prevalence) of children with clinical pneumonia and NP carriage of VT pneumococci. The contrast between the two groups will be presented as a prevalence ratio (and 95% confidence intervals), with ratios expressed as the prevalence in the 1+ 1 group compared to the prevalence in the 3 + 0 group. To account for cluster-level non-independence, the primary analysis will use generalised estimating equations (GEE) with a log link, binomial family and exchangeable correlation structure. The GEE models will adjust for stratification variables, and age will be included in the model for the endpoint of VT carriage in unimmunised infants aged 6-12 weeks, due to rapid age-related changes in prevalence in the first months of life. Non-inferiority will be established if the upper limit of the confidence interval around the prevalence ratio is ≤1.38.

We have *a priori* interest to examine the following potential effect modifiers: (a) age (2–12 weeks, 13 weeks–9 months, 10–23 months and 24–59 months), (b) inpatient/outpatient status and c) severity (severe pneumonia defined as clinical pneumonia with O_2_ saturation < 92%). The number of cases of each endpoint in the subgroups above may not be sufficient to assess non-inferiority in those strata but may enable the detection of differences in effectiveness between groups. We will examine the strength of evidence for differences between subgroups using interaction tests.

A secondary exploratory measurement and analysis of the primary endpoint will be conducted in year 2 of the trial, in order to detect potential early development of superior impact in the 1 + 1 group. This secondary hypothesis is different to the primary hypothesis of non-inferiority and will use an alpha value of 0.05, as will the final analysis.

The secondary endpoints of community pneumococcal carriage will be measured in years 2 and 4 of the study while carriage in infants aged 6–12 weeks presenting for their first dose of PCV will be measured in year 4. Comparison of the two groups will be presented as a prevalence ratio (and 95% confidence intervals). The same analytical methods as the primary endpoint analysis will be used to account for cluster-level non-independence and the allocation of clusters. We will use the same non-inferiority measurement as the primary endpoint, where non-inferiority will be established if the upper-limit of the confidence interval around the prevalence ratio for VT carriage in the 1 + 1 versus 3 + 0 clusters is ≤1.38.

An exploratory analysis will be performed to measure the association between age-specific contact pattern frequencies and pneumococcal carriage. The association between physical and non-physical contact frequency and age-specific pneumococcal carriage will be analysed using GEE models.

The endpoints monitoring potentially different disease risk (incidence of clinical and radiological pneumonia, IPD and mortality) will be evaluated in semi-blinded safety analyses presented to the DMC at 1, 2, 3, and 4 years after initiation of the interventions. These will not be formal analyses and will not influence the risk of false positive results. These analyses will be concealed from the investigators. The DMC may choose to use the results from the exploratory measurement of the primary endpoint in Year 2 to initiate further safety analyses and measurement of the incidence of clinical pneumonia associated with NP carriage of VT pneumococci. The DMC may also use the results of the community carriage survey in year 2 to inform considerations of safety. These analyses will be concealed from the investigators.

The degree of evidence sufficient to justify early stopping of the trial may be complicated by different accrual rates and potential local epidemics in different clusters. Thus, within and between cluster information will be evaluated for the DMC’s deliberations. The disadvantages of stopping a trial early, such as lack of credibility, imprecision and bias, will be accentuated in cluster-randomised studies.

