### Criteria for discontinuing or modifying allocated interventions {11b}

Trial participants are discontinued from participation in the study if:
Any clinically significant adverse event, intercurrent illness, or other medical condition or situation occurs such that continued participation in the study would not be in the best interest of the participant.The parent or guardian so desires.

Participants who attend an EPI clinic outside their cluster and within the study area, but continue to reside in their original cluster, receive the trial schedule originally indicated on their infant welfare card and on the trial sticker. If participants migrate within the study area before completing their PCV schedule they continue to receive the trial schedule allocated in the cluster of their new residence (Table 2). Participants who migrate after completing their PCV schedule do not receive any further doses of PCV in the cluster of their new residence (Table 2). Parents in the 1 + 1 group are advised that if they migrate permanently out of the trial area they should attend the next available EPI clinic to complete the standard schedule for PCV. If an infant allocated to the 1 + 1 group visits an EPI clinic outside the study area the parent is instructed to request that their child receive the trial schedule indicated on the infant welfare card and study sticker. The study sticker includes free-call telephone numbers so that parents, or EPI staff outside the study area, may call for guidance. Infants resident in the alternative schedule clusters who decline consent are assigned to the national standard schedule.

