## Discussion

The start of recruitment in the trial was delayed 17 months in 2018/2019 during negotiation of the formal agreement with the MoH regarding the collaborative approach to the trial. Recruitment began on 22 August 2019. Enrolment in the trial was suspended for 4 months in 2020, from 26 March until 30 June, due to restrictions associated with the COVID-19 pandemic. Recruitment in the 1 + 1 clusters resumed from 1 July and was then again suspended on 5 August due to pandemic related restrictions. During these periods of suspension, participants who were already enrolled continued to receive the trial allocated schedules as recorded on infant health cards. The DMC, TSC, and Sponsor, deemed there was less risk to participants if MoH EPI staff followed the schedule indicated on the infant welfare card rather than ask EPI staff to administer PCV in a schedule contrary to that recorded on the infant welfare card. Attendance at immunisation clinics in the trial area was reduced for several months during this time but immunisation of infants was largely caught up when attendance returned to normal 3–4 months after the initial introduction of pandemic related restrictions. Clinical surveillance at health facilities was scaled back on 26 March to the two main hospitals and nursing staff were withdrawn from nine outlying clinics. Collection of NP swabs was suspended from 26 March–7 September and surveillance continued only for safety endpoints of hospitalisation and invasive pneumococcal disease. Disease surveillance was expanded site by site between 28 May and 3 August to then include all health facilities.

Infants resident in 1+ 1 villages who were not enrolled during the COVID-19 interruptions and who may have received the standard 3 + 0 schedule will constitute ‘cross-over’ between the two groups. Cross-over in 1 + 1 clusters will reduce any difference in effect between the two groups with a potential bias towards a null result. A formal evaluation in September 2020, of pandemic-related cross-over, found 1.6% of infants enrolled in the 1+ 1 group were cross-overs during this period while the proportion of all cross-overs in the 1+ 1 group since the beginning of the trial was 4.4%, primarily related to decline of consent. We project that in year 4 of the trial total cross over in the 1 + 1 group will be 3–4%. Formal statistical simulations indicated that such cross-over will have a negligible impact on study power, statistical coverage, or bias.

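### The written cross-over definition omits 1+1 residents who stay in their cluster and receive the 3+0 schedule, although the Discussion counts such infants and names decline of consent as the main source of its 4.4%

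*Protocol article*

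**What the plan says.** Section {20a} of the protocol article (Statistical methods for primary and secondary outcomes) sets out two limbs. The first is residential: "Cross-over between groups will be defined as (a) change of residential location from a 1 + 1 to 3 + 0 cluster", or the reverse, lasting 4 months or more. The second concerns timing: "b) receipt of the third dose of PCV at 8 months of age or greater in a 3 + 0 cluster".

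Section {11b} says what happens to decliners in the experimental arm: "Infants resident in the alternative schedule clusters who decline consent are assigned to the national standard schedule". Table 2 likewise lists declined or withdrawn consent as a reason for not receiving the local 1+1 schedule.

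The Discussion then uses the term more widely. It says that 1+1 residents "who were not enrolled during the COVID-19 interruptions and who may have received the standard 3 + 0 schedule will constitute" cross-over. It reports that the proportion of all cross-overs in the 1+1 group "since the beginning of the trial was 4.4%, primarily related to decline of consent". It continues: "We project that in year 4 of the trial total cross over in the 1 + 1 group will be" 3–4%, and says simulations showed that such cross-over has a negligible effect on power, statistical coverage and bias. On direction it states: "Cross-over in 1 + 1 clusters will reduce any difference in effect between the two groups with a potential bias towards a null result".

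**The concern.** Within the 1+1 arm, the definition in {20a} can be met only by moving house. The protocol itself creates another route from 1+1 to 3+0, through declined or withdrawn consent and through non-enrolment. The Discussion identifies declined consent as the main source of the cross-over observed so far. The limbs are also lopsided. A 3+0 resident whose late third dose may act like a booster is counted, but there is no mirror limb for a 1+1 resident given the three-dose series.

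What is at stake is the year-4 cross-over rate. The reassurance in the Discussion rests on a projected total of 3–4%. That projection can be checked only if the year-4 rate is counted in the same way. A rate computed as {20a} is written would leave out the largest known component and look lower than it is. By the Discussion's own account, this cross-over pulls the arms together, which in a non-inferiority trial is the direction that favours the claim.

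**Working it through.** **Reproducing the plan's figure.** The 4.4% cannot be recomputed. The Discussion gives no numerator, denominator or split by reason. The related pandemic figure of 1.6% is expressed as a share of infants enrolled in the 1+1 group, although the infants concerned were not enrolled, so its base is also unclear.

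**Setting the definition against its use.** Reading the two limbs as alternatives, which is the generous reading, the infants in question fare as follows:

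| Infant | Limb (a), moves for 4+ months | Limb (b), late third dose in a 3+0 cluster | Treated as cross-over in the Discussion |
|---|---|---|---|
| 1+1 resident, consent declined, stays, receives 3+0 | No | No: lives in a 1+1 cluster | Yes: main reason for the 4.4% |
| 1+1 resident, not enrolled in the COVID-19 suspensions, stays, receives 3+0 | No | No: same reason | Yes, explicitly |
| 1+1 resident who moves to a 3+0 cluster for 4+ months | Yes | Not needed | Not singled out |

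Limb (b) does not rescue the definition, because it is restricted to 3+0 clusters.

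**Size of the omission.** The only inputs are the 4.4% and the statement that it was mainly due to declined consent. Assume that mainly means more than half, that each infant is classed by one reason, and that decliners did not also move between arms.

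- Decliners: more than 0.5 × 4.4 = 2.2 percentage points.
- Left under {20a} as written: less than 4.4 − 2.2 = 2.2 percentage points.

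Non-enrolled infants who stayed put would also drop out, so the literal rate would be lower still. How much lower cannot be derived, because the documents do not say whether the 1.6% overlaps with decliners or shares their base. No literal year-4 figure can be derived either, because the projection is not split by reason.

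**Scale of the cross-over itself.** As an illustration, assume direct dilution only: a share c of 1+1 children carries at the 3+0 risk. The observed prevalence ratio is then 1 + (true ratio − 1) × (1 − c). For a true ratio at the margin of 1.38:

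- c = 3%: 1 + 0.38 × 0.97 = 1.369
- c = 4%: 1 + 0.38 × 0.96 = 1.365
- c = 4.4%: 1 + 0.38 × 0.956 = 1.363

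This is small. It depends on how many infants cross over, not on how they are labelled.

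**The case against.** The strongest reply is that nothing inferential depends on the definition. Section {20c} analyses clusters by random allocation, forms the per-protocol set from coverage thresholds, and uses compliance with the allocated schedule as the sensitivity term. Relabelling infants changes neither the prevalence ratio nor its comparison with 1.38. That stands, and it confines the point to one descriptive rate.

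A second reply is that practice is already right. The September 2020 evaluation evidently included decliners, and the Discussion calls the non-enrolled infants cross-over. On a plain reading, the projection and the simulations used the wider meaning. This also has force: the documents give no sign that year 4 will be counted differently. But it shows that {20a} is the section that is wrong. A rule stated as what will be done should match what is done, and an analyst following it would obtain a different rate.

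A third reply is that annual coverage is reported "as the proportion of surviving, resident children, who have completed the respective schedules at the ages of 12 and 18 months", so a decliner given 3+0 appears as not having completed 1+1. That is only a partial substitute, because the same figure also contains infants whose booster was missed or late.

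Stronger readings are tempting. A reader might infer that the statement of negligible impact is unsound or that the non-inferiority conclusion is biased by the definition. The documents support neither, because the projection appears in the same section that counts these infants and the estimate does not use the definition. A reader might also fault {20c} for not defining the denominator of the compliance term, but that is detail commonly left to the statistical analysis plan, which is not shown.

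**Conclusion.** The point holds as a contradiction within one document, and {20a} is wrong as written. Applied literally, it would omit most of the 4.4%, leaving less than 2.2% under the assumptions set out in the working. A year-4 rate on that basis could not be compared with the projected 3–4%. The consequence is limited to this reported rate. It is worth correcting because cross-over in this arm favours non-inferiority and the year-4 rate is the natural check on the projection.

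**What to change.** Add a third limb to the definition in {20a}:

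> (c) a resident of a 1+1 cluster, enrolled or not, who receives the standard schedule (three PCV13 doses, at any age) for any reason, including declined or withdrawn consent or non-enrolment.

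The limb should carry no upper age. Clinic doses are often late, and an age limit of 8 months would miss a delayed third dose in a 1+1 cluster, which limb (b) does not catch. State also that:

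- each infant is counted once, even if more than one limb applies;
- infants dosed before the intervention began, or given the booster in the 4-month catch-up, are reported separately;
- the denominator is all resident infants of 1+1 clusters.

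Report the year-4 rate on this definition beside the projected 3–4%. The cost is one limb and a few clarifying phrases. No new data are needed: section {19} has trial staff at every EPI clinic recording immunisations for all infants, and the Discussion already counts these children.

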#### Participant selection

The sampling frame for selection to receive the interventions will be all infants resident in the 68 selected clusters. Residency is defined as:
Born to or cared for by a parent or guardian who is resident for greater than 4 months as confirmed by BHDSS records or a household visit with the report of the household or compound head. Provisional residency may be established by the verbal report of the parent or guardian.Born to or cared for by a parent or guardian who intends to be resident for greater than 4 months with verification at a household visit and report of the household or compound head. Provisional residency may be established by the verbal report of the parent or guardian.

The sampling frame is developed and continually updated as part of the FWHDSS and BHDSS. Pregnancies and births in all households are registered from 4-monthly enumerations of each household, village reporter records, and registration at EPI clinics. These data are electronically recorded in the field and synchronised centrally on a weekly basis. A verified and updated sampling frame is available for use each week. The sampling frame lists the mother’s name, infant’s name, date of birth, father’s name, name of household head, village name, compound number and individual ID number.

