## Assignment of interventions: allocation

### Sequence generation {16a}

Sixty-eight PVS trial clusters were randomised using a blocked scheme to ensure similar numbers of clusters were assigned to each group. Randomisation was stratified by a binary variable correlated with ‘high’ or ‘low’ cluster-level incidence of clinical pneumonia. Randomisation was carried out in permutations using the above stratification until selections achieved balance in terms of presence of a health centre and balance on population size between the two groups. In order to select the stratifying variable of cluster-level incidence of clinical pneumonia, cluster-level prevalence of ‘high’ or ‘low’ VT carriage in children with clinical pneumonia in the BHDSS was correlated with: clusterwise population density, rates of hospitalisation, clinical pneumonia, radiological pneumonia, IPD and mortality. Of the five listed outcomes, clinical pneumonia incidence had the closest correlation with VT carriage prevalence and thus was chosen as the stratifying variable.

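### The carriage GEE models are stated to adjust for the stratification variables, but not for health-centre presence and population size, on which allocation was also constrained

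*Protocol article*

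**What the plan says.** On allocation, the protocol article (Sequence generation {16a}) states: "Randomisation was stratified by a binary variable". The variable is high or low cluster-level incidence of clinical pneumonia. Allocations were then redrawn "until selections achieved balance in terms of presence of a health centre and balance on population size between the two groups". The Concealment mechanism section adds that the final list was drawn at random from 100 valid lists.

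On analysis, the article (Statistical methods for primary and secondary outcomes {20a}) specifies GEE "with a log link, binomial family and exchangeable correlation structure" and then says: "The GEE models will adjust for stratification variables". No other covariate is named for the primary endpoint. The same sentence goes on to say that "age will be included in the model for the endpoint of VT carriage in unimmunised infants aged 6-12 weeks", giving the reason "due to rapid age-related changes in prevalence in the first months of life". Further on, the section reuses the primary methods for the secondary carriage endpoints, saying that they serve "to account for cluster-level non-independence and the allocation of clusters".

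**The concern.** Three cluster-level factors shaped the allocation. The stated covariate set clearly covers only one of them.

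Forcing balance on a factor that predicts the outcome makes the estimated prevalence ratio less variable from one possible allocation to another. A robust standard error from a model without that factor does not see this. It leaves the factor's contribution in the between-cluster residuals and so overstates the uncertainty. The non-inferiority verdict depends on whether one upper confidence limit is at or below 1.38, so an overstated standard error costs power.

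**Working it through.** **Inputs from the article (Sample size {14}).** Prevalence 13% in both arms, margin 1.38 on the prevalence ratio with a one-sided 95% limit, ICC 0.02, 60 children per cluster, 68 clusters, design effect 1 + 59 × 0.02 = 2.18, 1980 per arm, stated power 93%. The article mentions 11 fixed health centres; I assume that they lie in 11 of the 68 clusters.

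**The plan's own figure.** Effective size per arm is 1980/2.18 = 908. On the absolute scale the standard error is √(2 × 0.13 × 0.87/908) = 0.0158. A margin of 0.38 × 0.13 = 0.0494 gives Φ(0.0494/0.0158 − 1.645) = 93.1%, and a margin of 0.05 gives 93.6%. So 93% reproduces on that scale. The decision rule is on the ratio scale, where the standard error of the log ratio is √(2 × 0.87/(0.13 × 908)) = 0.121 and power is Φ(0.322/0.121 − 1.645), about 84%. The simulations below use the ratio scale, so their power starts near 85% rather than 93%.

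**How much could be gained.** The between-cluster share of the variance is 60 × 0.02/2.18 = 55%. If the omitted factors explain a fraction r of the between-cluster variance, the interval width is multiplied by about √(1 − 0.55r): 0.972, 0.943 and 0.914 for r = 0.1, 0.2 and 0.3. The documents give no value for r.

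**Simulation.** There were 3000 trials per row, each with 68 clusters of 60 and ICC 0.02. Allocation was stratified and constrained on both factors (health-centre counts as even as 11 allows, mean size within 0.1 SD; both tolerances are assumed). The model was log-link with Poisson variance and a robust standard error corrected for leverage. The assumed effects on log prevalence were: none; 0.15 for a health centre and 0.08 per SD of size (moderate); 0.30 and 0.20 (strong).

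The share of between-cluster variance is 0.13 × V/(0.02 × 0.87). Here V = (size effect)² + (health-centre effect)² × (11/68)(57/68). V is 0.0064 + 0.0225 × 0.1356 = 0.0095 in the moderate case, a share of about 7%. It is 0.04 + 0.09 × 0.1356 = 0.0522 in the strong case, about 39%.

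| Strength | Strata-only: mean reported SE / actual SD | Adjusted: mean reported SE / actual SD | Width ratio | Power, strata-only → adjusted | One-sided error at ratio 1.38, strata-only → adjusted |
|---|---|---|---|---|---|
| None | 0.1194 / 0.1211 | 0.1195 / 0.1211 | 1.00 | 85.7% → 85.7% | 5.1% → 4.9% |
| Moderate | 0.1194 / 0.1176 | 0.1172 / 0.1176 | 0.98 | 86.4% → 86.8% | 4.8% → 5.4% |
| Strong | 0.1197 / 0.1085 | 0.1054 / 0.1064 | 0.88 | 87.2% → 92.0% | 3.2% → 4.9% |

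The Monte Carlo error on the last column is about √(0.05 × 0.95/3000) = 0.4 percentage points. Only the 3.2% therefore departs clearly from 5%.

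The actual SD shows that the constraint itself delivers most of the precision: in the strong case it is 0.1085 without adjustment and 0.1064 with it. Adjustment mainly brings the reported standard error into line.

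**Need for a correction.** With no prognostic effect, the uncorrected robust standard error falls from 0.1167 to 0.1150 when the two covariates are added, although the actual SD stays at 0.1211. Without a small-sample correction, part of any apparent gain would be spurious.

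**The case against.** The strongest objection is that the covariate list belongs in the statistical analysis plan, which the article says the Trial Steering Committee will approve. The plural in the adjustment sentence, and the later remark on accounting for the allocation of clusters, also leave room for the balancing factors. This stands in part: the text does not exclude them, and a plan that already names them settles the point. But the article does state a covariate set, its randomisation section names only one stratifier, and neither balancing factor appears anywhere as a covariate.

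It is also fair that the gain is unproven. A reader might infer that the planned interval is wider than it needs to be. The documents do not support that as fact: they give no association between carriage and either factor, and with no association nothing is gained. The stratifier was also chosen because, among the candidates examined, it correlated most closely with vaccine-type carriage, and it is already in the model.

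A reader might further infer that age belongs in the primary model, since it is used for the 6–12 week endpoint and date of birth is held. That does not follow:

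- The stated reason concerns the first months of life. That window contains the whole infant sample but only part of a sample running to 59 months.
- Age acts on the within-cluster 45% of the variance. For two assumed age patterns explaining 0.8% and 2.5% of the outcome variance, the interval narrows by only 0.2% and 0.6%.
- The children are pneumonia cases presenting after years of intervention, so their age mix may itself respond to the schedule.
- Age is a planned effect modifier. Collapsibility of the ratio therefore does not guarantee that adjustment leaves the estimand unchanged.

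**Conclusion.** The point holds as a mismatch between design and stated analysis, with a conditional cost. If health-centre presence and population size predict cluster-level carriage, the strata-only standard error is too large and the test is conservative. Across the assumed strengths, adjustment narrows the interval by 0% to about 12%. The upper end needs the two factors to explain about 40% of between-cluster variance; a moderate association gives about 2%.

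The omission threatens power only. At the margin the strata-only error was 5.1%, 4.8% and 3.2%, so there is no sign of inflated false non-inferiority. These figures rest on equal clusters of 60, ICC 0.02, 11 health-centre clusters and the assumed balance tolerances. The change is worth making because it costs almost nothing and matches the analysis to the allocation.

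**What to change.** State that the GEE models for the carriage endpoints adjust for the stratification variable, presence of a health centre and cluster population size, with a small-sample correction to the robust standard error. Name a Poisson working model with robust standard errors as the fallback if the log-binomial model does not converge. Keep the strata-only model as a sensitivity analysis. Leave age out of the primary model; at most, report an age-adjusted sensitivity analysis. Settle this before year-4 carriage data are analysed by group, so that the covariates cannot be chosen on the result.

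The cost is wording in the analysis plan. Both variables were used to screen the allocations and are therefore already held. The downside is a slightly more complex model and two degrees of freedom at cluster level, out of 68 clusters.
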